## Assignment of interventions: allocation

### Sequence generation {16a}

Computer-based randomisation will be used (www.random.org/lists/), via a numbered sequence, in both studies, by blinded researchers. Allocation of women who underwent chemotherapy and those who did not will be proportionate among the groups (stratified randomisation).

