## Statistical methods

### Statistical methods for primary and secondary outcomes {20a}

#### General analytic procedures

The superiority of the Mind programme over the control group(s) will be tested through the analysis of changes in the primary (cancer-specific QoL) and secondary outcomes (anxiety and depressive symptoms, psychological flexibility, self-compassion, health-related QoL, resources consumption), controlling for sociodemographic and clinical variables and potential moderation effects of variables such as the awareness of psychological processes, the frequency of at-home practice, the number of major life events occurring during the previous year and efficacy expectancy. The Mind programme will be compared against the support group in study 1 and against both the support and treatment as usual (waiting list) groups in study 2. Study 1 also includes immunological and epigenetic markers as secondary outcomes. The analytical approaches for both studies are otherwise comparable.

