#### Analyses by aims

Aim 1: Determine the efficacy of the Mind programme compared to an active (i.e. support group) and/or inactive (i.e. treatment as usual group) control condition at post-intervention and at 6-month follow-up period.

The planned analysis for each outcome is a repeated-measures linear mixed model, including polynomial simple slopes to identify non-linear change over time. Within-group and contemporaneous between-group post hoc comparisons, using independent- or paired-samples *t*-tests (as appropriate), adjusted for multiple comparisons using the modified Bonferroni adjustment, will be performed. The efficacy of the intervention can be inferred through the evaluation of the simple slopes for each treatment condition, whereby the experimental condition demonstrates a significant improvement in QoL scores over time, and this improvement exceeds that of the control condition. The clinical significance of changes presented by each participant will be determined by computing the reliable change index (RCI) and considering mixed models of repeated measures (i.e. growth modelling analysis). In the former, we will calculate primary or secondary outcome RCI for each participant between pre- and post-intervention, as well as pre-intervention and 6 months. An RCI of ± 1.96 is considered statistically significant at *p* = 0.05, and the proportions of participants within each treatment condition who demonstrate significant improvement, decline and no change will be recorded. Fisher’s exact test will be used to examine for significant differences in the proportion of change between treatment allocations. Finally, we will perform correlation analysis between the raw RCI values and demographic variables separately for each treatment condition. This final analysis is used to examine potential predictors of individual change and the nature of that change.

Aim 2: Determine the cost-effectiveness of the Mind programme compared to an active (i.e. support group) and/or inactive (i.e. treatment as usual group) control condition at post-intervention and at 6-month follow-up period.

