#### Covariates (controlling variables)

Where variables are expected to correlate with but not differentially predict outcomes, we will control for the influence of expected covariate variables by including them at the baseline model. The planned covariates consist of sociodemographic and clinical variables, such as age, education level, marital status, type of BC, BC stage, previous chemotherapy treatment, use of psychopharmacological medication, time since diagnosis, recurrence and number of major life events occurring during the previous year.

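### The covariate adjustment planned for the mixed model is not carried through to the visit-specific arm differences in mean score, which are tested by raw post hoc t-tests

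*Protocol article*

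**What the plan says.** All references are to the Protocol article.

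- **General analytic procedures ({20a})**: superiority is to be tested "controlling for sociodemographic and clinical variables and potential moderation effects of variables".
- **Covariates (controlling variables)**: "we will control for the influence of expected covariate variables by including them at the baseline model". The list includes "type of BC, BC stage, previous chemotherapy treatment, use of psychopharmacological medication, time since diagnosis, recurrence".
- **Sequence generation {16a}**: "Allocation of women who underwent chemotherapy and those who did not will be proportionate among the groups (stratified randomisation"). The stratifier is therefore also one of the planned covariates.
- **Analyses by aims, Aim 1**: the time points of interest are given by "control condition at post-intervention and at 6-month follow-up period". The main analysis is stated as follows: "The planned analysis for each outcome is a repeated-measures linear mixed model, including polynomial simple slopes to identify non-linear change over time". Then come within-group and "contemporaneous between-group post hoc comparisons, using independent- or paired-samples" t-tests, under a modified Bonferroni adjustment. On how to conclude, the section says: "The efficacy of the intervention can be inferred through the evaluation of the simple slopes for each treatment condition". Improvement in the Mind arm must be significant and must exceed that of control.
- **Sample size {14}**: study 1 quotes a detectable between-group difference at follow-up of SMD 0.51. Study 2 assumes SMD 0.5 for Mind against waiting list at 6 months. Both calculations are described as being for a linear mixed model.

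**The concern.** Aim 1 asks about efficacy at two visits, and the sample size section quotes an arm difference at follow-up. The test named for that difference in means is an ordinary two-sample t-test on the scores at that visit. It has no place for the planned covariates, the baseline score or the chemotherapy stratum, and it does not draw on the correlation between visits that the mixed model estimates.

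Two things are at stake. The first is precision: prognostic information that is collected, and already used in the main model, is left out of the follow-up comparison. The second is consistency: a report could show an adjusted model result beside an unadjusted 6-month p-value for the same outcome, and the two could differ only because their covariate sets differ.

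**Working it through.** **Inputs from Sample size {14}.** Study 1: 75 per group, 10 to 30% attrition, alpha 0.05, 80% power, compound symmetry with rho = 0.5, SMD 0.51. Study 2: 2:2:1 allocation, N = 117 before the attrition allowance, SMD 0.5.

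**Assumptions.** Two-sided alpha (sidedness is not stated). The share of variance explained by covariates, R² = 10%, 20% or 30%. The correlation of chemotherapy with quality of life, r = 0.2, 0.3 or 0.4. Attrition of 20% as the central case, so 75 × 0.8 = 60 per arm.

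**1. Reproducing the SMD of 0.51.** It can be reached in two ways.
- Group-by-time F test, N = 150, no attrition, 2 and (150 − 2) × 2 = 296 degrees of freedom: 80% power needs f ≈ 0.255 (noncentrality 150 × 0.255² ≈ 9.75), so 2f ≈ 0.51.
- Plain two-sample comparison with 60 per arm: power 0.798 (normal) or 0.791 (t). The detectable SMD is 0.511 or 0.516.

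The figure therefore does not show which test the authors had in mind. The text ties it to the mixed model.

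**2. Power of the raw t-test against an adjusted contrast at one visit, study 1.** The noncentrality is SMD × √(n/2) for the raw test and SMD/√(1 − R²) × √(n/2) after adjustment. With n = 60, √(n/2) = 5.477.
- Raw: 0.51 × 5.477 = 2.79, power 79%.
- R² = 10%: 0.538 × 5.477 = 2.94, power 83%.
- R² = 20%: 0.570 × 5.477 = 3.12, power 87%.
- R² = 30%: 0.610 × 5.477 = 3.34, power 91%.
- Baseline score with rho = 0.5 (R² = 0.5² = 0.25): 0.589 × 5.477 = 3.23, power 89%. A simulation of 20,000 trials gave 0.788 raw against 0.886 adjusted.

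Across the stated attrition range, 10% to 30% (67.5 to 52.5 per arm), the raw test has 84% to 74% power and the baseline-adjusted contrast 92% to 85%.

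These figures are at alpha 0.05, before the modified Bonferroni adjustment. As an illustration, at alpha 0.025 with 60 per arm they are about 70% raw and 83% baseline-adjusted. The levels fall and the gap remains.

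**3. Study 2, Mind against waiting list.** The arms are 117 × 2/5 = 46.8 and 117 × 1/5 = 23.4. At SMD 0.5, power is 50% by raw t-test and 61% with baseline adjustment, if rho = 0.5. That rho is assumed, since the study 2 correlations are not given. Only the gap bears on this point.

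**4. Ignoring the chemotherapy strata alone.** When the strata are balanced by design, the true standard error is about √(1 − r²) times the one the t-test uses. The actual size is therefore 2 × [1 − Φ(1.96/√(1 − r²))].
- r = 0.2: 1.96/0.980 = 2.00, about 4.5%.
- r = 0.3: 1.96/0.954 = 2.05, about 4.0%.
- r = 0.4: 1.96/0.917 = 2.14, about 3.2%.

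All are below 5%. The test is mildly conservative, not invalid.

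**The case against.** The strongest reply is that the adjusted analysis is the main one, and this stands. Aim 1 makes the mixed model the planned analysis for every outcome, the covariates (previous chemotherapy among them) belong to that model, the t-tests are labelled post hoc, and efficacy is to be inferred from the model's slopes. A reader might infer that the plan abandons its adjusted analysis at the decisive contrast. The text does not support that.

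A reader might also infer that the trials are sized on the unadjusted t-test. The sample size section names a linear mixed model for both studies, and 0.51 is reproduced by a group-by-time test at N = 150 as well as by a two-sample comparison. Nor is the t-test the only visit-specific comparison of arms: reliable change from baseline to each later assessment is compared by Fisher's exact test. That compares proportions of responders, not means.

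The power gaps accordingly belong to the follow-up t-tests, not to the trials' main analysis. No false-positive risk follows from ignoring the strata. Complete-case t-tests could be exposed to selective dropout, but section {20c} plans imputation that could also feed them, so no bias is claimed.

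It can also be said that extracting contrasts is a matter for an analysis plan not shown here. That does not remove the point, because the article does not leave the method open: it names the t-test. With three assessments, linear plus quadratic time by arm already fits every visit mean, so the planned model can supply the same differences.

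**Conclusion.** The point holds in a limited form. The covariate adjustment promised for the superiority comparison is not carried through to the mean arm differences at post-intervention and 6 months, because the only test named for them is a raw independent-samples t-test. The adjusted mixed model remains the main analysis.

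The cost is precision and consistency: about 4 to 12 percentage points of power at these comparisons for assumed R² of 10% to 30%, and about 10 points for baseline adjustment at rho = 0.5, with 60 per arm, SMD 0.51 and two-sided alpha 0.05 before the multiplicity adjustment. The R² values, the 20% attrition and the chemotherapy correlations are assumptions. The correlation of 0.5 between visits is the article's own for study 1.

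**What to change.** In Analyses by aims, Aim 1, replace the independent- and paired-samples t-tests with contrasts from the fitted mixed model: the arm difference at post-intervention and at 6 months, and the within-arm change, each with a 95% confidence interval. Keep the modified Bonferroni adjustment. State that:

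- time is modelled so that each visit mean is free (visit as a factor, or linear plus quadratic time by arm);
- the baseline outcome score is used in the model;
- the listed baseline covariates are included;
- chemotherapy status is always retained, because it is the stratifier.

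It would also help to say whether the 6-month difference or the slope decides efficacy. There is no added cost beyond wording: the model is already being fitted, and no further data or participants are needed.

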### Primary outcome

#### Cancer-specific QoL

The European Organization for Research and Treatment of Cancer Quality of Life Questionnaire (EORTC QLQ-C30; [39]; Portuguese version: [40]) is a 30-item questionnaire that reflects the multidimensionality of the QoL construct, comprising five functional subscales (physical, role, cognitive, emotional and social); a global health/QoL subscale; three symptom subscales (fatigue, pain and nausea/vomiting); single items for the assessment of additional symptoms commonly reported by cancer patients (dyspnoea, appetite loss, sleep disturbance, constipation and diarrhoea); and one more item related to the perceived financial impact of cancer and cancer treatment. All the items are scored on a 4-point Likert type scales ranging from 1 (not at all) to 4 (very much), except the two items of the global health/QoL subscale, which use a modified 7-point linear analogue scale. The 23-item Supplementary Questionnaire Breast Cancer Module (QLQ-BR23) additionally assesses body image, sexual function, sexual enjoyment and future perspective. In the Portuguese validation study, global QoL presented a Cronbach’s alpha of 0.88 and the different subscales presented Cronbach’s alpha ranging between 0.57 and 0.88 [41].

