### Methods in analysis to handle protocol non-adherence and any statistical methods to handle missing data {20c}

All main analysis will be performed as an intention-to-treat (ITT) analysis to provide unbiased estimates of the intervention efficacy regarding the level of participants’ adherence to the study. In such an approach, the participants will be considered according to the group they were originally assigned to regardless of intervention compliance. Missing data will be reported and when MCAR (Missing Completely at Random) or MAR (Missing at Random) occurs, multiple imputation methods will be used to estimate missing values when appropriate. Missing values will be imputed with well-established methods that reduce bias in estimates such as multiple imputation, full information maximum likelihood and empirical Bayes estimation, or multiple imputations with chained equations (MICE), if a substantial amount of missing data exists.

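### The efficacy criterion requires significance only of the Mind arm's own improvement and attaches no test to the between-arm difference

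*Protocol article*

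**What the plan says.** The Aim 1 text (Statistical methods {20a}, Analyses by aims) sets out three things in turn.

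- The model: "The planned analysis for each outcome is a repeated-measures linear mixed model, including polynomial simple slopes to identify non-linear change over time".
- Post hoc comparisons within and between arms, "using independent- or paired-samples *t*-tests (as appropriate), adjusted for multiple comparisons using the modified Bonferroni adjustment, will be performed".
- The criterion. Its basis is the slope of each arm taken separately, and it is met in the case "whereby the experimental condition demonstrates a significant improvement in QoL scores over time, and this improvement exceeds that of the control condition".

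Elsewhere the protocol points towards a comparison of the randomised arms. General analytic procedures states: "The superiority of the Mind programme over the control group(s) will be tested through the analysis of changes in the primary" and secondary outcomes. Sample size {14} powers study 1 on a between-group difference in cancer-specific quality of life at follow-up (SMD 0.51), and study 2 on Mind against waiting list at 6 months (SMD 0.5).

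The primary outcome is described as "comprising five functional subscales (physical, role, cognitive, emotional and social); a global health/QoL subscale", together with symptom scales, single items and the breast module. No one score is singled out for the criterion.

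**The concern.** A superiority trial should rest on a test of the difference between randomised arms. In the stated criterion, the word for significance belongs to the Mind arm's own change over time. The second half, that the improvement exceeds control's, has no test, alpha or interval.

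A within-arm change mixes any treatment effect with whatever happens to all participants. Change common to both arms is plausible here. Study 1 recruits at the start of radiotherapy and follows women to 6 months. Study 2 enrols from 2 months before radiotherapy to 6 months after it. If quality of life recovers in everyone, the first half of the criterion is met without any effect, and the second half becomes a matter of which arm's mean happens to be larger.

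The headline conclusion of both trials rests on this criterion, and so does the decision on which intervention is later offered to the waiting-list arm.

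**Working it through.** **Inputs.** From Sample size {14}: study 1 has 75 per arm, attrition 10 to 30%, alpha 0.05 (sidedness not stated; two-sided assumed), compound symmetry with rho = 0.5. At 20% attrition, 75 × 0.8 = 60 per arm. Study 2 needs N = 117 at 2:2:1, so about 47 Mind (117 × 2/5 = 46.8) and 23 waiting list (117 × 1/5 = 23.4). *Assumption:* a common improvement D in both arms, in baseline SD units. The protocol gives neither its size nor its direction, so a range is shown.

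**The plan's own figure.** A two-arm comparison at one visit with 60 per arm has a detectable SMD of (1.960 + 0.842) × √(2/60) = 0.51. A repeated-measures F calculation with N = 150, two groups and three measures also gives f = 0.255, that is SMD = 2f = 0.51. So the stated 0.51 reproduces, and it describes a between-arm test.

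**The literal criterion under no treatment effect.** A change score has variance 2(1 − rho) = 1, so each arm's mean change has standard error 1/√n. With equal arms, let z0 = t(0.975, n−1) − D√n. The chance that Mind's change is significantly positive and also numerically larger than control's is approximately

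P = ∫ from z0 to ∞ of φ(z)Φ(z) dz = [1 − Φ(z0)²] / 2.

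Worked case, n = 60, D = 0.3: z0 = 2.001 − 0.3 × 7.746 = −0.323; Φ = 0.373; P = (1 − 0.139)/2 = 0.430.

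| D (SD) | z0 (n = 60) | P, formula | P, simulated |
|---|---|---|---|
| 0 | 2.001 | 2.2% | about 2.5% |
| 0.1 | 1.226 | 10.4% | 11% |
| 0.2 | 0.452 | 27.3% | 27% |
| 0.3 | −0.323 | 43.0% | 43% |
| 0.5 | −1.872 | 50.0% | 50% |

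The formula treats the variance as known, hence the small gaps at low D. The ceiling of 50% is structural: once Mind's own change is almost always significant, exceeding control is a coin toss.

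**Other settings, simulated.**
- Study 1, 75 per arm: 12.6%, 31.8%, 46.0% and 50% at D = 0.1, 0.2, 0.3 and 0.5.
- Study 1, 52 per arm (about 30% attrition): 40.1% at D = 0.3 and 49.8% at 0.5.
- Study 2, Mind 47 against waiting list 23: 21.1%, 35.6% and 49.2% at D = 0.2, 0.3 and 0.5.
- Three-wave slopes instead of change scores (60 per arm, visits assumed at 0, 2 and 8 months): 41.5% at D = 0.3.

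**A direct between-arm test of the change.** In the same simulations it rejects in Mind's favour in about 2.5% of trials at every D from 0 to 0.6.

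**Precision of the separate t-tests.** With a true effect of 0.51 SD at both post-baseline visits, power at follow-up is about 0.79 for an unadjusted t-test and 0.89 with baseline adjustment (60 per arm), or about 0.87 and 0.95 (75 per arm).

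**The case against.** The best defence is that the protocol intends a tested difference. It says efficacy can be inferred, which is softer than a formal decision rule. Slopes by condition normally come from a group-by-time model. General analytic procedures promises a superiority test, and the sample size rests on a between-group difference. If the slope difference is tested inside the mixed model, the error rate is controlled. This stands as a limit on the concern: the inflation belongs to the literal reading. It does not remove the point, because no section names the contrast that decides efficacy, and the one criterion that is stated omits it.

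A second objection is that the inflation depends on an assumed common improvement and vanishes when there is none. That is correct, and the rates are conditional on D.

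Three stronger readings may tempt a reader.

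- *The t-tests contradict intention-to-treat or are complete-case.* The documents do not support this. The comparisons ("Within-group and contemporaneous between-group post hoc comparisons, using independent- or paired-samples" t-tests) are post hoc and multiplicity-adjusted. The statement "All main analysis will be performed as an intention-to-treat (ITT) analysis" is explained as analysis by assigned group, which a t-test by arm satisfies. The same section plans multiple imputation, and t-tests can be run on imputed data.
- *The t-tests inflate false positives.* They do not. A between-arm t-test at one visit is a valid randomised comparison; it only loses precision when baseline is ignored.
- *The many QLQ-C30 scales multiply the error rate.* That would need any one scale to suffice without correction, which the protocol does not say. It is a separate matter from the slope criterion.

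**Conclusion.** The concern holds as a defect in the stated criterion: significance is required of the within-Mind improvement only, and the between-arm difference carries no test. At 60 per arm, with rho = 0.5, no treatment effect and equal improvement in both arms, following the text literally would support efficacy in about 2.5%, 11%, 27%, 43% and 50% of trials at a common improvement of 0, 0.1, 0.2, 0.3 and 0.5 SD, against about 2.5% for a direct test. The result rests on the literal reading, on two-sided alpha of 0.05 and on the assumed common improvement.

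A reader might infer that the trials will in fact claim false efficacy up to half the time. The documents do not support that: they also promise a superiority test, and a tested slope difference would keep the error rate in check. What can be said is that the current wording permits the faulty inference and does not match the quantity on which the trials are powered.

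**What to change.** Replace the criterion under Aim 1 with the model-based between-arm difference in change, taken from the group-by-time terms of the planned mixed model with baseline accounted for, reported at 6 months with a 95% confidence interval and p-value:

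- **Study 1:** Mind versus support.
- **Study 2:** Mind versus waiting list, which is the powered contrast, and Mind versus support.
- **Post-intervention contrasts:** secondary, in both studies.

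Apply this to one named QLQ-C30 score. Take the between-arm comparisons at each visit from the same model instead of separate t-tests; this gains precision and is not a repair of false positives. Label within-arm slopes descriptive.

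Time may be categorical or polynomial: with three visits, linear and quadratic terms by arm fit the same means. The cost is a wording amendment, best made before outcome data are compared by arm. No new data or different model is needed.

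In the simulations, adding the between-arm test returns the false efficacy rate to about 2.5% at every common improvement examined.

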### Sample size {14}

Regarding study 1, power was considered according to a sensitivity analysis of the likely attainable sample size and compare with the effect sizes estimated by previous meta-analyses and studies suggesting improvements in mood and QoL between SMD = 0.2 to 0.6, favouring psychotherapies over controls [15, 16]. It is anticipated that up to *N* = 150 (*n* = 75 per group) participants will be recruited, and attrition rates of between 10 and 30% can be expected. The planned analysis specifies a repeated-measures linear mixed models analysis, a group allocation of 1:1, alpha of 0.05, a minimum of 80% power, three assessment points and a compound symmetry correlation matrix (rho = 0.5; Lu et al., 2008). Under these parameters, the study is powered to reliably detect a between-group difference on cancer-specific QoL at follow-up of SMD = 0.51 (WebPower; [37]).

For study 2, the GLIMMPSE software was used to calculate the minimum sample size required for a three-armed linear mixed model with three measurements. Assuming a comparable effect size to that estimated in study 1 (SMD = 0.5) favouring the Mind intervention group over waiting list at 6 months for QoL, an unstructured correlation matrix, a group allocation of 2:2:1, alpha of 0.05 and a minimum of 80% power, the minimum sample size required is *N* = 117. To account for up to 30% attrition, this sets the minimum total sample size at *N* = 153 [38].

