### Recruitment {15}

In study 1, women being treated for BC in the Radiotherapy Service of CHUC will be invited to participate. The point of recruitment will be at the beginning of radiotherapy treatment. The trial will be introduced to potential participants by their radiotherapy physician. A screening interview will be conducted with interested patients to assess eligibility and obtain written informed consent.

In study 2, the trial will be disseminated among the Portuguese population via press releases, social media platforms (e.g. postings with relevant groups and communities via Facebook and Instagram) and BC patients’ associations electronic distribution lists. Women with BC will register their interest by completing a form hosted on a secure online platform, which can be easily found in the project’s website. Alternatively, interested persons can contact research staff via email provided in the study advertisements. A screening interview, conducted by phone call, is later conducted to assess eligibility and obtain electronic informed consent.

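### The Aim 1 efficacy rule requires a significant before-after improvement within the Mind arm, which can hide a real benefit if quality of life falls in both arms; its comparison with control has no test attached

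*Protocol article*

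**What the plan says.** The Aim 1 text (Statistical methods {20a}, Analyses by aims) plans a repeated-measures linear mixed model for each outcome. It then lists "Within-group and contemporaneous between-group post hoc comparisons, using independent- or paired-samples *t*-tests (as appropriate), adjusted for multiple comparisons using the modified Bonferroni adjustment". The inference on efficacy comes next: "The efficacy of the intervention can be inferred through the evaluation of the simple slopes for each treatment condition". The same sentence then sets out the pattern that those slopes must show, in two conditions: "whereby the experimental condition demonstrates a significant improvement in QoL scores over time, and this improvement exceeds that of the control condition".

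Three other places bear on this:

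- General analytic procedures, at the start of the same section: "The superiority of the Mind programme over the control group(s) will be tested through the analysis of changes in the primary" and secondary outcomes. No test is named there.
- Sample size {14}: study 1 is powered on a between-group difference in cancer-specific QoL at follow-up (SMD 0.51), with "alpha of 0.05, a minimum of 80% power, three assessment points". The correlation structure assumed across the visits is stated as "compound symmetry correlation matrix (rho = 0.5"). Study 2 is sized on SMD 0.5 for Mind over waiting list at 6 months.
- Recruitment {15}, study 1: "The point of recruitment will be at the beginning of radiotherapy treatment". Under Eligibility criteria {10}, study 2 enrols women from 2 months before radiotherapy starts to 6 months after it ends.

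**The concern.** The Aim 1 sentence is the only place where the protocol says how efficacy will be inferred, and it sets two conditions.

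The first, significant improvement within the Mind arm, uses no control data. It mixes the programme's effect with whatever would have happened anyway. The section on the choice of comparators says that the control arms are there to take account of time effects; this condition sets that aside. A woman's QoL may well change between the baseline and 6-month assessments for reasons unrelated to the programme. If the shared movement is downwards and Mind softens it, the randomised comparison favours Mind but the Mind arm does not improve significantly on its own baseline, so the rule is not met.

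The second condition is the randomised comparison, but as worded no significance level, contrast or time point goes with it.

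At stake is whether the primary conclusion of both trials has the power and error rate implied by the sample size section.

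**Working it through.** **Inputs from the protocol (Sample size {14}).** 75 per arm in study 1, attrition 10 to 30%, alpha 0.05 (taken as two-sided), power 80%, correlation 0.5 with compound symmetry, SMD 0.51 at follow-up.

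**Assumed.** Normal outcomes with SD 1; a change over time, shared by the arms, whose direction and size the protocol does not give, so a range is shown.

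**Step 1: reproduce the stated 0.51.** The SD of change is √(2(1 − 0.5)) = 1, so the change contrast and the follow-up contrast have the same precision. Minimum detectable SMD = (1.960 + 0.842) × √(2/n):

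- n = 75: 0.457
- n = 67.5 (10% loss): 0.482
- n = 60 (20% loss): 0.511
- n = 52.5 (30% loss): 0.547

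The stated figure is reproduced at 60 per arm. That it rests on 20% attrition is an inference; the text does not say so. The main results below use 60 per arm.

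**Step 2: the within-arm hurdle.** If control declines by d and the true effect is 0.51, Mind's mean change is 0.51 − d and its paired t statistic is centred on about (0.51 − d) × √60. The critical value is about 2.00.

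- d = 0: 0.51 × 7.746 = 3.95, so the hurdle is passed in about 97% of trials
- d = 0.3: 0.21 × 7.746 = 1.63, about 35%
- d = 0.5: 0.01 × 7.746 = 0.08, about 3%

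**Step 3: simulate the whole rule.** 400,000 trials per setting; paired t-test within Mind (two-sided 0.05, improving direction), combined either with a significant between-arm t-test in favour of Mind (strict reading) or with Mind's mean change merely larger than control's (literal reading).

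True SMD 0.51, 60 per arm, probability of a positive conclusion:

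| Control declines by | Between-arm test alone | Two-part rule, strict | Two-part rule, literal |
|---|---|---|---|
| 0 | 79% | 79% | 97% |
| 0.1 SD | 79% | 75% | 88% |
| 0.2 SD | 79% | 61% | 66% |
| 0.3 SD | 79% | 35% | 36% |
| 0.4 SD | 79% | 13% | 13% |
| 0.5 SD | 79% | 3% | 3% |

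If control recovers by 0.2 SD instead, the strict rule keeps the full 79%. With all 75 per arm, the between-arm test has 87% power and the strict rule 72%, 43% and 3% at declines of 0.2, 0.3 and 0.5 SD.

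No true effect, both arms recover equally, 60 per arm:

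| Shared recovery | Literal | Strict | Between-arm test alone |
|---|---|---|---|
| 0 | 2.4% | 0.8% | 2.5% |
| 0.1 SD | 11% | 1.8% | 2.5% |
| 0.2 SD | 27% | 2.4% | 2.5% |
| 0.3 SD | 43% | 2.5% | 2.5% |
| 0.5 SD | 50% | 2.5% | 2.5% |

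The literal rate cannot pass about 50%, because Mind must also be ahead of control.

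These are t-tests on change from baseline to 6 months, standing in for slopes from a three-visit mixed model. The percentages would move somewhat under the model, but the mechanism would not change.

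**The case against.** The strongest reply is that the sentence is explanatory. It says that efficacy *can* be inferred, not that it will be concluded only in this way. It follows directly after a mixed model and multiplicity-adjusted between-group comparisons, General analytic procedures promises a test of superiority, and study 1 is powered on a between-group difference. Read in that setting, the excess over control probably means a significant excess, and the false-positive rate then never passes 2.5%. The exact test behind it could also stand in an analysis plan that is not shown. This stands, and the 27 to 50% figures hold only under the literal reading.

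A reader might go further and infer that the trials do not test the randomised comparison at all, or that natural recovery alone yields a positive result. The documents do not support either. Exceeding control is the randomised comparison, between-group tests are planned, and Mind must be ahead of control under any reading.

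It is also fair to say that the power loss needs a decline from baseline to 6 months, and that nothing in the protocol shows one. The recruitment and eligibility text makes a shared change plausible but gives neither its direction nor its size.

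What the reply does not remove is the within-arm condition. It is written into the only stated criterion, no reading of the comparison with control takes it away, and the planned between-group tests are called post hoc and are not tied to the conclusion.

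**Conclusion.** The point holds in two parts of unequal strength.

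1. **Firm under any reading:** the within-arm condition adds a hurdle that the power statement does not cover. Its cost is negligible if QoL is stable or recovers, and runs from 4 percentage points (79% to 75%) to nearly all the power (79% to 3%) for control declines of 0.1 to 0.5 SD, under the strict reading with 60 per arm, correlation 0.5 and SMD 0.51. The steepest figure needs a decline that almost cancels the assumed effect.
2. **Conditional on wording:** the comparison with control has no test attached. Only if it is taken as numerically larger does the error rate rise with shared recovery; the more plausible intended meaning keeps it at or below 2.5%.

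Since a between-arm difference is what study 1 is powered on, and the harm depends on an undocumented natural course, this should be fixed but does not undermine the trials' design. General analytic procedures describes the two studies' analyses as otherwise comparable, so the correction applies to both.

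**What to change.** Replace the efficacy sentence in Aim 1 with wording such as: *Efficacy is concluded only from the between-arm (group-by-time) contrast in change in cancer-specific QoL from baseline to the 6-month follow-up, estimated from the mixed model, two-sided 0.05, in favour of Mind. In study 2 this contrast is against [named comparator]. No within-arm test forms part of the criterion.* Within-arm changes are then reported descriptively with confidence intervals.

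Six months is the time point to which the study 2 sample size refers, and the natural reading of *follow-up* in study 1. In study 2 the team should choose the comparator knowing that the sample size was calculated for Mind against waiting list.

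Under the assumptions above, the false-positive rate in favour of Mind is then 2.5% and power at SMD 0.51 is 79% with 60 per arm (87% with 75, 73% with 52), whatever course the arms share. The cost is one or two sentences in the protocol and analysis plan, ideally before the data are unblinded. No new data are needed.
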